### Ethics statement

2.2.

The Clinical Trial and Biomedical Ethics Committee of the Affiliated Hospital of Qingdao University has approved this trial. During the clinical trial, any protocol modifications must be filed with and approved by the Ethics Committee. Before participation, members of the research team will explain the study verbally and in writing and obtain each participant’s written informed consent. An investigator will completely and comprehensively describe the study purpose and methods, the drug’s effects, reasonably expected benefits, possible side effects, and potential risks to the participant or their designated agent. This clinical trial follows the Declaration of Helsinki, Good Clinical Practice (GCP) for Drug Clinical Trials as issued by the State Drug Administration, and other relevant regulations. It is registered in the China Clinical Trial Registration Center (ChiCTR2300069044).

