### Sample size calculation

2.6.

The sample size was calculated based on the primary outcome. According to previous studies, the incidence of severe postoperative pain in patients undergoing TKA with multimodal analgesia is 25–40% (16, 17). Considering variance in multimodal analgesia and follow-up times, we reviewed the records of 20 patients who had undergone unilateral TKA in the past month. With multimodal analgesia, 48% of patients reported severe pain (NRS ≥ 7 points) within 12 postoperative hours. Therefore, we assumed that the incidence of rebound pain in patients undergoing TKA in the context of multimodal analgesia is 45%. We expect that the incidence of rebound pain in the esketamine group will be at least 35% lower than in the placebo group during the first 12 post-surgical hours. Using Power Analysis and Sample Size version 15.0 (Stata Corp. LP, College Station, TX, United States) and assuming a significance (*α*) level = 0.05 and power (1 − *β*) = 80% determined sample sizes for the esketamine group (*N*_1_) = 160 and placebo group (*N*_2_) = 160. Considering potential withdrawal (10%), a final 356 patients (178 in each group) will be included to achieve the appropriate power to test our hypothesis.

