TKA surgery in our center is expected to last 1–1.5 h. Due to the controlled use of psychotropic drugs, we plan to administer esketamine by continuous infusion at 0.3 mg/kg/h during surgery. This dose is lower than the specified dose in the manual and has analgesic and anti-hyperalgesia effects without causing adverse reactions like separation anesthesia. To ensure investigator and participant blinding and reduce mental symptoms, all participants will receive midazolam 0.05 mg/kg after spinal anesthesia. Before the operation, all participants will receive 0.5 mg of phenazopyridine hydrochloride (Chengdu List Pharmaceutical Co., Ltd., Chengdu, Sichuan, China) to antagonize the effect of esketamine on the M-cholinergic receptor.

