### Strategies to improve intervention adherence

2.13.

At the recruitment and screening stage, the investigator will describe the study purpose, drug intervention, research protocol, trial process, drug delivery plan (including dose, delivery method, and time period), clinical assessments, sampling frequency, biological sample collection, potential risks and benefits of participation, and compensation, to ensure each participant is fully informed before they volunteer, and to enhance participant adherence. Before the participant begins the trial, the anesthesiologist, quality controller, and drug administrator will carefully check their participant number, randomization group, dosage, and pump speed. After the intervention, these investigators will carefully count the remaining research drugs, empty packages, and drug delivery devices.

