### Standard analgesia procedure

2.14.

Each participant will be given 200 mg of celecoxib orally the day before their surgery. Twenty minutes before the end of the operation, the anesthesiologist will administer 4 mg of ondansetron (Qilu Pharmaceutical Co., Ltd., Jinan, Shandong, China). After the procedure, a PCIA device will be connected, loaded with 100 μg of sufentanil (Yichang Renfu Pharmaceutical Co., Ltd., Yichang, Hubei, China), 8 mg of ondansetron, and 5 mg of butorphanol tartrate (Jiangsu Heng Rui Medicine Co., Ltd., Jiangsu, China), diluted to 100 ml with normal saline. The background PCIA dose will be 1 ml/h, the single press dose will be 2 ml, the locking time 15 min, and the maximum infusion rate is 10 ml/h.

In the post-anesthesia care unit (PACU), when the participant’s NRS is ≥4 points (i.e., they require analgesics), the anesthesiologist will administer 50 μg of fentanyl (Jiangsu Nhwa Pharmaceutical Co., Ltd., Xuzhou, Jiangsu, China) intravenously as remedial the analgesia. The subsequent dose will be half of that preceding, at a between-rescue analgesia dose interval of ≥20 min. When the NRS of the participant is <4 points, the remedial analgesia is considered effective. In the surgical ward, the participant will receive flurbiprofen axetil 50 mg (Beijing Taide Pharmaceutical Co., Ltd., Beijing, China) twice daily and acetaminophen oxycodone (Fujian Minglong Pharmaceutical Co., Ltd., Longyan, Fujian, China) three times daily as the basic analgesic. The standard of care is to initiate the remedial analgesia procedure when the participant’s NRS is ≥4, at which time they are administered an intravenous injection of 50 mg of pethidine (Qinghai Pharmaceutical Factory Co., Ltd., Xining, Qinghai, China), which can be repeated every 4–6 h, for a maximum daily dose of 300 mg. In case of moderate to severe nausea or vomiting after the operation, 4 mg of intravenous ondansetron will be administered.

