### Safety outcomes

3.3.

(1) nausea and vomiting; (2) respiratory depression (i.e., blood oxygen saturation < 93%); (3) hypertension (i.e., blood pressure > 30% of baseline value); (4) hypotension (i.e., blood pressure < 30% of baseline value); (5) tachycardia (i.e., heart rate > 100 beats/min); (6) bradycardia (i.e., heart rate < 50 beats/min); (7) nervous system complications (restlessness, delirium, nightmare, restlessness); (8)increased secretions; (9) nerve injury caused by regional block or local anesthetic poisoning; (10) wound infection, deep vein thrombosis, or pulmonary embolism.

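### Section 2.12 orders phenazopyridine for every participant as a muscarinic blocker, a purpose the named drug does not fit; check the drug name and correct it (minor)

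*Protocol article*

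**What the plan says.** The order stands at the end of section 2.12 (Interventions) of the protocol article, just after the choice of esketamine infusion rate and the midazolam given to protect blinding. It says that, before surgery, "all participants will receive 0.5 mg of phenazopyridine hydrochloride". It names the maker as "Chengdu List Pharmaceutical Co., Ltd., Chengdu, Sichuan, China" and gives one reason: "to antagonize the effect of esketamine on the M-cholinergic receptor". Drug, dose, recipients, maker and purpose are therefore all in a single sentence.

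Phenazopyridine is not mentioned again in the article, and neither is the M-cholinergic receptor. Section 3.3 (Safety outcomes) lists "increased secretions" among the events to be recorded, without linking it to this premedication. Section 2.6 (Sample size calculation) gives the number of people the order would cover: "a final 356 patients (178 in each group) will be included".

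**The concern.** The sentence matches a drug to a pharmacological task. Antagonizing an effect at the muscarinic receptor is the work of an antimuscarinic. Phenazopyridine is generally known as a urinary-tract analgesic and is not an antimuscarinic. If that is right, the drug and its stated purpose do not belong together, and the likeliest explanation is that another product's name was mistyped or mistranslated.

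This is a dosing instruction in the description of the trial regimen, not background text. Someone who followed it to the letter would give a drug that does not provide the blockade the protocol wants, and someone repeating the regimen from the article would copy the same name. The stakes are the correctness and reproducibility of a co-medication given to everyone, not the estimate of the treatment effect.

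**Working it through.** No formula applies, because the question is whether a drug name fits its stated use. The check sets the relevant statements side by side.

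1. **Drug and dose.** Section 2.12: phenazopyridine hydrochloride, 0.5 mg.
2. **Recipients.** Section 2.12: all participants, hence both arms. By section 2.6 that is 2 × 178 = 356 planned.
3. **Purpose.** Section 2.12: to oppose esketamine's action at the M-cholinergic receptor. No second purpose is given.
4. **What the purpose requires.** A drug with antimuscarinic action.
5. **What the named drug is.** The article does not say. From general drug-class knowledge it is a urinary-tract analgesic without antimuscarinic action. This is the one input from outside the documents, and it is treated here as an assumption.
6. **Whether the rest of the article settles it.** It does not. The drug is named nowhere else, and no other text describes it as antimuscarinic or gives it a different role. Recording increased secretions as a safety outcome (section 3.3) fits an intended antimuscarinic premedication. That is context only and does not show that the name is wrong.

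Items 3 to 5 give the result: if the assumption in item 5 holds, the named drug cannot serve the stated purpose.

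**Effect on the statistics.** The premedication does not differ by arm (item 2). The drug name does not enter the sample size calculation in section 2.6 or the modified Poisson models in section 7, so there is no figure to reproduce and none that changes when the name is corrected.

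**The case against.** The strongest objection is that the mismatch depends wholly on a fact the documents do not contain. Without the drug's class, section 2.12 reads as one coherent sentence, and no two statements in the article contradict each other. The second half is correct: this is not an internal contradiction, and it is not presented as one. The first half does not defeat the point. A drug's class is ordinary professional knowledge, not a recalled figure or the result of a particular study, and it is labelled here as an assumption for the sponsor to check.

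A second objection is that the slip may exist only in the article. Site staff work from the approved protocol and pharmacy order, which may carry the right name. This stands, and it is why the point is minor and the fix starts with a check. The published sentence would still need correcting.

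Three stronger readings are tempting but unsupported:

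- *Participants will in fact receive the wrong drug.* The article cannot show what the approved protocol or the pharmacy order says.
- *The safety results are distorted.* The article gives no basis for sizing any change in secretions, heart rate or another event, and both arms are treated alike.
- *Other sections confirm the error.* The drug is absent from the analgesic regimen in section 2.14, but a correctly named antimuscarinic would not be listed there either, and midazolam, also given to everyone, is not. The checks listed in section 2.13 say nothing about whether the name is right.

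**Conclusion.** The point holds as a minor drug-name correction to one sentence in section 2.12. It rests on a single assumption, that phenazopyridine has no antimuscarinic action. Given that, the order as written names a drug that cannot do the job assigned to it, for all 356 planned participants. The randomized comparison, sample size and primary analysis are unaffected, and no change in any outcome rate is claimed. No dosing error is shown either: the 0.5 mg needs checking only because it is attached to a doubtful name. A reader may feel able to guess the intended product, but the documents do not identify it and this review does not.

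**What to change.** Compare the drug name and the 0.5 mg dose in section 2.12 with the ethics-approved protocol and the pharmacy order; the manufacturer given in the sentence helps to identify the product. Replace the name with the antimuscarinic that was intended. If the slip is only in the article, a published correction is enough. If the approved protocol has the same name, section 2.2 applies, under which "any protocol modifications must be filed with and approved by the Ethics Committee".

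The cost is one check against two documents, one corrected name and, only in the second case, one ethics filing. No analysis, sample size or schedule changes.

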### Strategies to improve intervention adherence

2.13.

At the recruitment and screening stage, the investigator will describe the study purpose, drug intervention, research protocol, trial process, drug delivery plan (including dose, delivery method, and time period), clinical assessments, sampling frequency, biological sample collection, potential risks and benefits of participation, and compensation, to ensure each participant is fully informed before they volunteer, and to enhance participant adherence. Before the participant begins the trial, the anesthesiologist, quality controller, and drug administrator will carefully check their participant number, randomization group, dosage, and pump speed. After the intervention, these investigators will carefully count the remaining research drugs, empty packages, and drug delivery devices.

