### Double blinding

2.8.

This study will follow a double-blind design. According to the allocation protocol, participants will be randomized to receive a continuous infusion of esketamine or 0.9% normal saline during the operation. To ensure investigator blinding, the drug administrator ([name]) will prepare syringes (Weigao Group Medical Polymer Products Co., Ltd., Weihai, Shandong, China) in a separate room, labeling them A or B. One syringe will be filled with 50 mg of esketamine and 0.9% of normal saline (20 ml total) and the other will be filled with the same volume of 0.9% normal saline. The appearances of syringes A and B will be identical, other than label. The drug administrator will be unaware of the distribution plan and the intervention measures accepted by the participants. Because esketamine has sedative and hypnotic effects, to prevent unblinding the investigators and participants, all participants will be given preoperative 0.05 mg/kg intravenous midazolam. Throughout data collection, nurses, surgeons, outcome assessors, and statistical analysts will all be unaware of participant treatment group assignments. An independent data and safety supervision committee will monitor the trial, without disclosing participant grouping, until completion of statistical analyzes.

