### Interventions

2.12.

Placebo group participants will receive an intravenous infusion of 0.9% normal saline (Weigao Group Co., Ltd., Weihai, Shandong, China). The infusion pump (Henan Tuoren Medical Equipment Group Co., Ltd., Changheng, Henan, China) mode is constant speed pumping, and the pumping time is from the end of the intraspinal anesthesia administration to the knee joint suture. The anesthesiologist can choose the appropriate medication protocol according to clinical practice, but other NMDA receptor antagonists, such as dextromethorphan and amantadine, will not be used.

Esketamine group participants will receive an intravenous infusion of esketamine (Jiangsu Heng Rui Medicine Co., Ltd., Jiangsu, China) following a standard dilution protocol [2 ml (50 mg) esketamine with 0.9% normal saline to 20 ml, 2.5 mg/ml]. The infusion rate of esketamine is 0.3 mg/kg/h, the mode of the infusion pump is constant speed pumping, and the infusion time is from the end of the spinal anesthesia administration to the knee joint suture. Drug managers need to monitor that the maximum dose of esketamine is not more than 0.5 mg/kg.

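### Sections 2.8 and 2.13 contradict each other on investigator blinding: the preparer called unaware, and the anesthesiologist, both check each participant's group

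*Protocol article*

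**What the plan says.** Section 2.8 (Double blinding) describes its measures as serving the blinding of investigators. Midazolam, for example, is given to everyone "to prevent unblinding the investigators and participants". The drug administrator prepares the syringes "in a separate room, labeling them A or B"; one holds esketamine and the other the same volume of saline. The section then says of this person: "The drug administrator will be unaware of the distribution plan and the intervention measures accepted by the participants". Surgeons, nurses, statistical analysts and those assessing outcomes are listed as unaware of allocation. Anesthesiologists are not on that list.

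Section 2.13 (Strategies to improve intervention adherence) says that before a participant starts, "the anesthesiologist, quality controller, and drug administrator will carefully check their participant number, randomization group, dosage, and pump speed". After the infusion, "these investigators will carefully count the remaining research drugs, empty packages, and drug delivery devices".

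Three other sections bear on this. In 2.7 the quality controller opens the allocation envelope. In 2.12 the paragraph on the placebo group says: "The anesthesiologist can choose the appropriate medication protocol according to clinical practice", apart from other NMDA antagonists. In 2.14 the anesthesiologist gives fentanyl rescue in the PACU.

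**The concern.** The article gives the same people two incompatible positions. Section 2.8 treats investigators, and the drug administrator by name, as blind. Section 2.13 calls the drug administrator, quality controller and anesthesiologist investigators and has them check the group and account for the drug.

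The anesthesiologist's position matters most. The primary outcome (3.1) is a self-reported move from NRS 3 or below to NRS 7 or above within 12 hours, and analgesia given during and soon after surgery can affect it. An anesthesiologist who knows the arm could, without intending to, give different co-medication in the two arms. The resulting bias could go either way and could not be undone afterwards.

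**Working it through.** No figure in the plan depends on this point, so the check sets the statements side by side and tests each under the two possible meanings of group.

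**Drug administrator**

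- Facts from 2.8: this person fills one syringe with esketamine and one with saline and attaches the labels A and B. This person therefore knows what each label contains.
- Read alone, 2.8 can be consistent: the drug administrator makes both syringes and someone else, such as the quality controller with the envelope, picks one.
- Section 2.13 closes that reading, because the drug administrator also checks the participant's group.
  - If group means the arm by name, the treatment is known directly.
  - If group means only A or B, the treatment is known because this person labelled the syringes.
- Under either meaning, the statement in 2.8 that this person is unaware cannot hold together with 2.13.

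**Anesthesiologist**

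- If group means the arm by name, the check unblinds the anesthesiologist.
- If group means only A or B, the check alone does not. Two routes remain:
  - Counting afterwards. If only the assigned syringe is prepared for each participant, esketamine packaging exists in one arm only and the count shows the arm. If both syringes are prepared for everyone, the packaging looks the same in both arms and the count need not show it. The article does not say which applies.
  - The labels. Only two are described, with no participant-specific code. If A and B keep their meaning throughout, learning the content once decodes every other participant.
- So the anesthesiologist may learn the treatment. The article neither confirms nor rules it out.

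**Quality controller**

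- This role opens the envelope (2.7) and checks the group (2.13). A role of this kind can properly be unblinded, but the article does not declare it so and 2.13 counts it among the investigators.

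**Extent**

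- The check in 2.13 applies to each participant: 2 × 178 = 356. For the drug administrator the contradiction arises every time. For the anesthesiologist the number cannot be derived, because it depends on what the check displays.

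**Where knowledge could act**

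| Step | Who | Room for discretion |
|---|---|---|
| Intraoperative co-medication (2.12) | Anesthesiologist | Open, apart from other NMDA antagonists |
| PACU rescue (2.14) | Anesthesiologist | Little: trigger, first dose, halving and interval are set |
| Ward rescue (2.9, 2.14) | Nursing staff, blinded | Not affected |
| Pain scores (2.9) | Participant, blinded | Not affected |

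The main route is therefore intraoperative co-medication.

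**The case against.** The strongest reply is that an unblinded preparer is compatible with a double-blind trial, that participants score their own pain, and that for the anesthesiologist group may mean only the syringe label. All of this stands. It limits the point but does not remove it: the article calls the preparer unaware, which 2.13 makes untrue, and it does not say what the anesthesiologist sees.

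It can also be said that PACU rescue follows fixed rules, and that intraoperative analgesic and sedative doses and steroid use are recorded and enter model 3. That makes an imbalance visible. It does not repair one, because these variables arise after randomization and would themselves be shaped by knowledge of the arm.

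A reader might infer from 2.12 that its rules need knowledge of the arm: the rate and the maximum ("Drug managers need to monitor that the maximum dose of esketamine is not more than" a stated amount) stand only in the esketamine paragraph, and the co-medication sentence only in the placebo paragraph. The documents do not carry that inference. Both paragraphs give the same pump mode and infusion window, the ban on other NMDA antagonists reads naturally as trial-wide, and the maximum is watched by drug managers rather than the anesthesiologist. This is paragraph layout, worth tidying, but not evidence of unblinding.

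The absence of anesthesiologists from the list in 2.8 is not a contradiction in itself, since that section promises blinding of investigators generally.

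**Conclusion.** The contradiction between 2.8 and 2.13 is real and lies in the text. If 2.13 is followed literally, the drug administrator is unblinded for all 356 planned participants, assuming only that the labels are not recoded between preparation and the check; no such step is described. The anesthesiologist may be unblinded, depending on what the check and the count reveal.

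Three stronger readings are tempting and not supported:

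- That the trial as a whole is not double-blind. Participants, surgeons, nurses, outcome assessors and analysts are all still described or treated as blinded, and nothing in 2.13 touches them.
- That every participant is treated by an anesthesiologist who has seen the allocation, or that one individual performs the check, chooses the drugs and gives rescue. The article names a role, refers elsewhere to anesthesiologists in the plural, and leaves the meaning of group open.
- That the bias can be sized. Any assumed drop in the 45% placebo rate through extra co-medication would be invented, and the direction is unknown.

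**What to change.** - **Section 2.8:** state that the drug administrator and quality controller are unblinded and have no part in anaesthesia, rescue, the pain diary or outcome data. Remove the statement that the drug administrator is unaware. Add anesthesiologists to the blinded roles.
- **Section 2.13:** take the randomization group out of the anesthesiologist's check and limit that check to participant number and pump setting on a coded syringe. Give the counting of drug and packaging to the two unblinded roles only.
- **Section 2.12:** reconcile the two paragraphs so that the infusion and co-medication instructions can be followed without knowing the arm. This concerns presentation only; no dose or clinical rule should change.

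The cost is a few sentences and a revised bedside checklist, using existing staff. Under section 2.2 the change must be filed with and approved by the ethics committee. Sample size, outcomes and analysis are untouched.
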